##### Exclusion criteria

Multiple pregnancyMaternal diseases (such as hypertension, diabetes mellitus, infections), pregnancy complications (such as pre-eclampsia or growth restriction) or use of medication that could interfere with placental transfer of the study drugContraindication to sildenafil therapy: renal or hepatic failure, maternal cardiac disease, hypotension (blood pressure < 90/60 mmHg), stroke, retinitis pigmentosa, sickle cell disease, bleeding disorders, active peptic ulcer, concomitant treatment with nitrates, previous serious adverse reaction or allergy to sildenafil, use of other vasodilator therapy, alpha-blockers, protease inhibitors, erythromycin or cimetidineHistory of psychiatric or psychological disease or concerns about psychological eligibilityPrevious loss of vision because of suspected non-arteritic, anterior, ischemic optic neuropathy (NAION)

#### Third trimester placenta transfer and safety study

##### Inclusion criteria

Singleton pregnancy with isolated fetal CDH, left- or right-sided, with any degree of lung hypoplasiaGestational age ≥ 36 + 6 and ≤ 40 weeksPlanned delivery at least 3 days after study initiationMaternal age ≥ 18 and ≤ 45 years (to allow consent and avoid age-related cardiac risks respectively)

##### Exclusion criteria

Multiple pregnancy, chromosomal or major structural fetal abnormalityMaternal conditions (such as hypertension, diabetes mellitus, infections), pregnancy complications (such as pre-eclampsia or growth restriction) or use of medication that could interfere with placental transfer of the study drugAny contraindication to sildenafil therapy as in sub-study 1Preterm premature rupture of membranes (pPROM)

### Interventions

In both sub-studies, sildenafil tablets will be administered orally to the mother as this administration route is the most practical and clinically most acceptable for sustained administration, especially in pregnant women. The half-life of sildenafil after oral administration is about 4 h [34]. Therefore, the most commonly used administration schemes for chronical conditions even in pregnancy consist in three administrations daily [20, 35–37].

Two sildenafil doses have been selected according to previously published literature and to our ex-vivo data on placental transfer [30], i.e., 25 and 75 mg. A dose of 25 mg three times daily has been proven safe in the treatment of pregnancies complicated by intrauterine growth retardation (IUGR) [24]. A dose of 75 mg three times daily is the maximum dose used in a trial on pregnant women affected by pre-eclampsia, without any fetal or maternal side effects being reported under that dose [23].

#### Second trimester placental transfer study (sub-study 1)

A single administration of sildenafil is planned before maternal and fetal blood sampling. Participants will be randomized to receive either a 25-mg or a 75-mg dose. For each dose, participating women will additionally be randomized to receive sildenafil either 2 h or 8 h before the termination. These time points have been selected because they represent the peak time and the trough time, respectively [34].

#### Third trimester placental transfer and safety study (sub-study 2)

Participants will be allocated to receive sildenafil tablets at a dose of 25 mg or 75 mg three times daily from 3 days prior to planned delivery until delivery.

The Standard Protocol Items: Recommendations for Interventional Trials (SPIRIT) Diagram in Fig. 1 summarizes trial procedures for sub-studies 1 (Fig. 1A) and 2 (Fig. 1B) [38]. For both sub-studies, collection of routine clinical information from participants’ medical records to determine eligibility, informed consent and patient randomization will take place during the screening visit. A web-based randomization tool will be used in order to assign each patient to a study arm.

**Fig. 1 Fig1:**
[figure not shown]
A; * − t_1_: screen visit; t0: allocation/baseline visit; t_1_: 2 or 8 h before termination of pregnancy; t_2_: at the time of feticide; t_3_: at patient’s discharge. B: * − t_1_: screen visit; t0: allocation/baseline visit; t_1_: 3 days before induction; t_2_: day 1 after first sildenafil administration; t_3_: 50 h after first sildenafil administration; t_4_: at beginning of labor; t_5_: at delivery; t_6_: day 1 after delivery; t_7_: at maternal and neonatal discharge

#### Second trimester placental transfer study (sub-study 1)

Eligible patients will be randomly assigned to one of four different study groups: dose 1 (25 mg) with sampling at 2 h, dose 2 (75 mg) with sampling at 2 h, dose 1 with sampling at 8 h or dose 2 with sampling at 8 hBaseline visit: maternal blood pressure, heart rate and oxygen saturation will be measured and Doppler examination of the fetal pulmonary circulation and umbilical artery will be performedDay 0: at the time of pregnancy termination, the same procedures as in the baseline visit will be performed. At this time point, one maternal and one fetal blood sample will be collected for analysis of sildenafil concentration

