#### Second trimester placental transfer study (sub-study 1)

We assume that a sample size of six participants per dose for each time point (total = 24 women) is an ethical balance between the research question and the exposure of healthy volunteers to the drug. In addition we will perform an interim analysis after having obtained all data in 16 women (four per group) to potentially conclude the study prematurely in case of a low variability (< 20% variability in fetal sildenafil concentrations) within the groups. To ensure a balance in sample size across groups over time, a block size randomization of 8 with equal numbers for each group is chosen [41, 42].

We expect a 2% incidence of maternal conditions representing an exclusion criteria for the study. Furthermore, since this is a study on pregnant women without medical conditions, we expect a high rejection rate (~ 50%). Since this is a short-term study, we do not expect any drop-out after allocation. Therefore, the plan is to assess a total of 49 women for eligibility for recruitment of up to 24 women.

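### In sub-study 1 the two 8 h groups (12 of 24 women) have no scheduled maternal vital signs at the 2 h time the protocol calls the peak

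*Protocol article*

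**What the plan says.** **Dosing and timing.** In the Protocol article, Interventions, the first sub-study 1 section gives a single dose 2 h or 8 h before termination and justifies the times: "These time points have been selected because they represent the peak time and the trough time, respectively". The later sub-study 1 section on visits defines four groups by dose and sampling time, beginning "dose 1 (25 mg) with sampling at 2 h, dose 2 (75 mg) with sampling at 2 h", followed by the same two doses at 8 h.

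**Tolerance endpoint.** Under Trial design, maternal tolerance in sub-study 1 is a secondary endpoint with two parts: change from baseline in blood pressure, heart rate and oxygen saturation, and incidence of side effects.

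**When vital signs are taken.** They are taken at the baseline visit. On the day of termination, "at the time of pregnancy termination, the same procedures as in the baseline visit will be performed". No other occasion is stated. The Fig. 1A legend lists screening, baseline, dosing ("2 or 8 h before termination of pregnancy"), feticide and discharge.

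**Sub-study 2.** The corresponding section schedules the same maternal measurements at 2 h and at 50 h after the first dose for every participant.

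**Analysis.** The Statistical analysis plan section summarises data by sub-study and dose group, calculates individual and mean changes from baseline, and is descriptive only.

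**The concern.** The fetal sample has to coincide with feticide, so in the 8 h groups it must sit at 8 h. Maternal blood pressure, heart rate and saturation carry no such constraint, yet they are tied to the same moment. Half of the women pass through the stated peak with no planned reading and are measured only at the stated trough. A fall in pressure that causes no symptoms and has resolved by 8 h would leave no trace in the planned data.

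Two things are at stake. First, the mean vital-sign change at the peak rests on half of the sub-study 1 women exposed to each dose. Second, if peak and trough readings are averaged within a dose group, a transient change is diluted. Maternal tolerance is a named secondary objective, and the Discussion presents the trial as a source of first data on maternal tolerance ahead of a larger trial.

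**Working it through.** **Inputs from the protocol**
- Size: "six participants per dose for each time point (total = 24 women"), under Sample size calculation, sub-study 1.
- Allocation: "a block size randomization of 8 with equal numbers for each group is chosen", same section.
- Interim: "interim analysis after having obtained all data in 16 women (four per group"), same section.
- Peak 2 h, trough 8 h: Interventions, sub-study 1.
- Half-life: "The half-life of sildenafil after oral administration is about 4 h", under Interventions.

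**1. The plan's own total.** 6 per cell × 2 doses × 2 sampling times = 24, as stated.

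**2. Women without a peak reading.** 8 h groups: 2 × 6 = 12 of 24 (50%), or 6 of 12 per dose. At the interim: 2 × 4 = 8 of 16, or 4 of 8 per dose.

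**3. Could another listed time point serve?** In the 8 h groups dosing is at 0 h, feticide at 8 h, and discharge later. Screening and baseline come before dosing. None falls near 2 h.

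**4. Level at 8 h relative to 2 h.** Assuming simple exponential decline from 2 h, the ratio is 2^(−(8−2)/t½).
- t½ = 4 h (stated): 2^(−1.5) = 0.354, about 35%.
- t½ = 3 h (assumed): 2^(−2) = 25%.
- t½ = 5 h (assumed): 2^(−1.2) = 44%.

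**5. Precision of the mean change at the peak.** The standard error is SD/√n. Going from 6 to 12 readings per dose multiplies it by √(6/12) = 0.71, whatever the SD.

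**6. Dilution if readings are averaged by dose only.** With equal numbers at each time, the pooled mean is (1 + r)/2 of the peak mean, where r is the 8 h effect as a fraction of the 2 h effect.
- If the effect is proportional to the level (assumption), r = 0.354 gives (1 + 0.354)/2 = 68% of the peak effect.
- If nothing remains at 8 h (assumption), r = 0 gives 50%.

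**7. Allowing for sub-study 2.** Its 12 women, 6 per dose, also have a 2 h reading after a first dose. Across the trial that makes 6 + 6 = 12 peak readings per dose now and 12 + 6 = 18 with the extra reading. If the two populations could be pooled, the standard error would be multiplied by √(12/18) = 0.82.

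**The case against.** The strongest reply is that the gap is narrow and partly filled elsewhere.

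- **Side effects are not tied to sampling.** A reader might infer that maternal tolerance as a whole is measured only at the moment of fetal sampling. The documents do not support that. Side-effect incidence is part of the endpoint, and adverse events are counted over treatment. This stands, and it limits the point to vital-sign changes without symptoms.
- **Sub-study 2 supplies peak readings.** A reader might infer that only 6 women per dose in the whole trial have peak data. In fact there are 12. This stands as a count, but sub-study 2 enrols women at 36+6 to 40 weeks carrying a fetus with diaphragmatic hernia, whereas sub-study 1 covers weeks 20.0 to 32.6 and other anomalies. It does not replace the earlier-gestation readings.
- **Event-detection figures prove little.** At an assumed 10% rate of peak hypotension, the chance of seeing at least one case is 1 − 0.9^6 = 47% with 6 readings and 1 − 0.9^12 = 72% with 12. A reader might take that as the loss. The protocol sets no such event and gives no rate; it analyses mean change. Counting sub-study 2 as well, the comparison becomes 72% with 12 against 1 − 0.9^18 = 85% with 18. The size of the point should not rest on these figures.
- **Dilution depends on the layout.** Changes are calculated at a time point, and an analysis plan that is not shown may split by sampling time. That would remove the dilution but would not recover the missing peak readings.
- **The article is condensed.** The Fig. 1A grid is not shown, and the full protocol may include post-dose monitoring. This is possible. However, the article states the sub-study 1 schedule, and the legend names its time points, none of them suitable.

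**Conclusion.** The point holds for vital signs. On the stated schedule, 12 of 24 women in sub-study 1 (6 of 12 per dose) have no planned blood pressure, heart rate or saturation reading at the peak. Their one post-dose reading comes at about 35% of the 2 h level, or 25% to 44% for an assumed half-life of 3 to 5 h. The cost is precision: in sub-study 1 the standard error of the mean peak change per dose could be 0.71 times what it will be. Averaging by dose alone could also shrink an apparent change to between 50% and 68% of its peak size under the stated assumptions.

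This is an inexpensive improvement to a secondary, descriptive endpoint. The primary endpoint and the sample size are unaffected. A reader might go further and conclude that the tolerance endpoint should be redefined as the 2 h change alone. Nothing in the protocol requires that; the reading at sampling is the one paired with a drug concentration and should stay. The conclusion rests on the schedule as printed in the article being complete for vital signs.

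**What to change.** In the sub-study 1 visit description under Interventions, and in Fig. 1A with its legend:

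1. Add maternal blood pressure, heart rate, oxygen saturation and a side-effect question at 2 h after the dose in the two 8 h groups.
2. Keep the existing readings at sampling in all four groups.
3. In the Statistical analysis plan section, state that vital-sign changes in sub-study 1 are reported by dose and time since dose, not pooled by dose.

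The cost is one extra set of non-invasive readings in 12 women, with no extra blood draw and no extra participants. The practical burden is that these women must be seen 2 h after the dose, and the article does not say where they are at that time. If the full protocol already schedules this reading, the visit description and the Fig. 1A legend should state it.

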#### Third trimester placental transfer and safety study (sub-study 2)

Participants will be randomly assigned to one of two study groups: dose 1 (25 mg three times daily) and dose 2 (75 mg three times daily)Baseline visit: the study procedures will involve measurements of maternal blood pressure, heart rate and oxygen saturation; fetal ultrasound for assessment of fetal wellbeing and Doppler examination of the fetal main pulmonary artery and contralateral pulmonary artery branch, mean cerebral artery, umbilical artery, ductus venosus; Doppler examination of the uterine arteries; fetal heart rate monitoring (cardiotocography)During sildenafil administration (from day 0 until occurrence of labor, specifically at 2 and 50 h after the first administration) the study procedures will be the same as in the baseline visit. Treatment compliance and any side effect will also be reported. One maternal blood sample will be collected on day 2 (50 h after the first administration) for determination of maternal plasma sildenafil concentrationDuring labor and at delivery fetal heart rate, maternal blood pressure, heart rate and oxygen saturation, and eventual side effects will be recorded as part of the clinical protocol. At the moment of delivery, one maternal and one umbilical cord blood sample will be collected for determination of sildenafil concentrationAt the neonatal follow-up visit (day 1 after birth), mean arterial blood pressure, vasoactive inotropic score [33] and early (< 24 h) lung function, expressed as Oxygenation Index and alveolar-arterial oxygen gradient will be recorded. Adverse effects, if any, will be recorded

### Sample size calculation

This is a phase II, dose-finding study and there is no information in the literature about transplacental sildenafil transfer in vivo. A formal power calculation has, therefore, not been performed [39, 40]. The number of cases is driven by the practices commonly used to document pharmacokinetics in a rather homogeneous population with simultaneous collection of maternal and fetal effects.

#### Second trimester placental transfer study (sub-study 1)

We assume that a sample size of six participants per dose for each time point (total = 24 women) is an ethical balance between the research question and the exposure of healthy volunteers to the drug. In addition we will perform an interim analysis after having obtained all data in 16 women (four per group) to potentially conclude the study prematurely in case of a low variability (< 20% variability in fetal sildenafil concentrations) within the groups. To ensure a balance in sample size across groups over time, a block size randomization of 8 with equal numbers for each group is chosen [41, 42].

We expect a 2% incidence of maternal conditions representing an exclusion criteria for the study. Furthermore, since this is a study on pregnant women without medical conditions, we expect a high rejection rate (~ 50%). Since this is a short-term study, we do not expect any drop-out after allocation. Therefore, the plan is to assess a total of 49 women for eligibility for recruitment of up to 24 women.

#### Third trimester placental transfer and safety study (sub-study 2)

To obtain reliable pharmacokinetic data, we plan to include six patients for each tested dose (total = 12 patients). For the reasons given above in sub-study 1, block randomization (block size = 4) will be used.

We expect a 50% incidence of maternal or fetal (i.e., not isolated cases, fetuses having had fetal therapy) conditions representing an exclusion criterion for the study and a 50% rejection rate. Speculating that the drop-out rate after inclusion will be less than 10%, we will need to assess for eligibility a total of 52 women with ongoing pregnancies and CDH at term.

The Data Safety and Monitoring Committee will evaluate drop-out rate ad interim, and is authorized to adjust sample size, if appropriate.

### Statistical analysis plan

For all pharmacokinetic, demographic, safety and efficacy outputs, data will be summarized by sub-study and dose group. For continuous variables, summary statistics will include the number of observations, the arithmetic mean, median, arithmetic standard deviation, minimum and maximum. For categorical variables, frequency counts and percentages will be used.

The measured sildenafil concentrations will be used to develop a physiologically based pharmacokinetic (PBPK) model allowing prediction of the maternal dose that will result in therapeutic concentrations in the fetus [43]. The effect of covariates (gestational age, maternal height and weight) will also be assessed.

For efficacy and tolerability endpoints, baseline is defined as the last value for each assessment prior to the subject’s first dose. Each individual change from baseline will be calculated by subtracting the individual subject’s baseline value from the value at the time point. The individual subject’s change from baseline values will be used to calculate the mean change from baseline. Missing values will not be imputed.

Adverse events will be summarized for each of the sub-studies and of the dose groups. Summaries will include the number of patients who have at least one occurrence of the adverse event. In addition, the total number of adverse events with a first reporting of the event while on treatment will be displayed. The analysis will be for descriptive purpose only and no inferential testing was performed.

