### Trial design

This is a randomized, investigator-blinded, double-armed, parallel-group, phase I/IIb study consisting of two different sub-studies recruiting simultaneously:Second trimester placental transfer study (sub-study 1)The primary outcome of this sub-study is the fetal plasma sildenafil level after oral administration maternally. Fetal plasma will be obtained by fetal cardiocentesis or cordocentesis, required for administration of the drugs used for feticide at the time of pregnancy termination [31, 32]. Maternal blood sampling will be performed simultaneously via peripheral venous puncture.Secondary endpoints are:Doppler ultrasound measures of pulmonary vasodilatation: change in the acceleration time/ejection time (AT/ET) ratio of the main fetal pulmonary artery and of the pulmonary artery branch closest to the ultrasound probe between baseline and the time of fetal blood sampling. Additional measures of blood flow resistance in the fetal main pulmonary artery and in the right and left pulmonary artery branch (Pulsatility Index, Resistance Index, peak systolic velocity, peak early diastolic reversed flow) will also be collectedEffect of sildenafil on the fetal systemic circulation: change in the Doppler waveform of the umbilical artery, between baseline and blood samplingSimulated maternal and fetal pharmacokinetic profilesMaternal tolerance, measured as change in blood pressure, heart rate and oxygen saturation compared to baseline, and incidence of side effects, including any kind of visual disturbanceThird trimester placental transfer and safety study (sub-study 2)The primary endpoint is sildenafil transfer at term, expressed as a ratio of the neonatal over the maternal sildenafil plasma concentration. Neonatal venous blood samples will be collected from the umbilical cord at delivery. Maternal blood sampling will be performed via peripheral venous puncture.Secondary endpoints are:Doppler ultrasound measures of pulmonary vasodilatation as described aboveEffect of sildenafil on the fetal systemic circulation: change from baseline in the Doppler waveform of the umbilical artery, mean cerebral artery, ductus venosus, change in fetal heart rate monitoring patternEffect of sildenafil on the maternal placental circulation: change from baseline in the Doppler waveform of the uterine arteriesSimulated maternal and fetal pharmacokinetic profilesMaternal tolerance measured as change in blood pressure, heart rate and oxygen saturation compared to baseline, and incidence of side effects, including any kind of visual disturbanceNeonatal tolerance, measured as trend in mean arterial blood pressure during the first 24 h of life, vasoactive inotropic score [33] at 24 h of life and early (< 24 h) lung function, expressed as Oxygenation Index and alveolar-arterial oxygen gradient

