The European Commission has supported the establishment of virtual thematic networks across Europe (European Reference Networks), aimed at sharing knowledge, exchanging information and facilitating collaborations between specialized centers. “ERNICA” is the European reference network on rare diseases of the foregut grouping skills from 20 centers in 11 countries. It covers malformations of the digestive system, the diaphragm (including CDH) and the abdominal wall. Such network will make a randomized clinical trial on CDH fetuses possible, despite the rarity of the condition. We also have already obtained Orphan Designation for this indication by the European Medical Agency (http://www.ema.europa.eu/docs/en_GB/document_library/Orphan_designation/2017/07/WC500231579.pdf). The present phase I/IIb trial should allow to determine the effective maternal dosage to be used in the subsequent phase III efficacy study. Moreover, it will investigate and provide first data on maternal and fetal tolerance and on the effect of the drug on the fetal pulmonary circulation. This knowledge will provide safety information also for other maternal and placental diseases, for which sildenafil is currently being explored.

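### Concentrations and the transfer ratio are summarised on the arithmetic scale and by dose only; geometric summaries with a 95% CI by randomised group would serve better (minor)

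*Protocol article*

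**What the plan says.** In the Protocol article, the Statistical analysis plan sets one rule for all outputs: "For all pharmacokinetic, demographic, safety and efficacy outputs, data will be summarized by sub-study and dose group". The list that it then fixes for anything measured on a continuous scale reads as follows: "summary statistics will include the number of observations, the arithmetic mean, median, arithmetic standard deviation, minimum and maximum". No geometric mean, log transformation or confidence interval is named in the article. For efficacy and tolerability it describes individual and mean change from baseline; no difference between doses is described. The section ends: "The analysis will be for descriptive purpose only and no inferential testing was performed". That sentence closes the adverse-event paragraph, so how far it reaches is unclear.

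The outcomes concerned are defined under Trial design. In sub-study 1, "The primary outcome of this sub-study is the fetal plasma sildenafil level after oral administration maternally". In sub-study 2 the primary endpoint is transfer at term, "expressed as a ratio of the neonatal over the maternal sildenafil plasma concentration".

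The group sizes are "six participants per dose for each time point (total = 24 women" in sub-study 1 and, for sub-study 2, "we plan to include six patients for each tested dose (total = 12 patients". The Sample size calculation section says that no formal power calculation was made. The measured concentrations also feed a physiologically based pharmacokinetic (PBPK) model that is to predict the maternal dose.

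**The concern.** Three features of the stated summary fit the primary outcomes badly.

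- **Scale.** Concentrations and their ratios cannot be negative and usually vary multiplicatively. An arithmetic mean of six ratios can be moved by one or two women with a low maternal level, and it does not invert: the mean of fetal/maternal is not the reciprocal of the mean of maternal/fetal. A mean and SD can also imply impossible negative values.
- **Precision.** The sample size has no precision basis, and the stated summaries give no interval. The reader is not told how well six women determine the primary estimate.
- **Grouping.** Sub-study 1 randomises to dose and to sampling at 2 h or 8 h, described as peak and trough. A summary by sub-study and dose merges the two times into a single mean and SD that describes neither.

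A related weakness concerns the Doppler and vital-sign outcomes. There is no placebo, so a mean change from baseline mixes any drug effect with time. The randomised 75 mg versus 25 mg contrast is the comparison least affected by this, and it is not described.

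At stake is how clearly the trial's main results are reported. The design and error rates are not affected.

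**Working it through.** **Inputs from the article.** Six women per dose and time point in sub-study 1 (4 × 6 = 24, or 2 × 6 = 12 per dose); six per dose in sub-study 2 (2 × 6 = 12). These totals agree with the text. Half-life is about 4 h (Interventions). There is no precision or power figure to reproduce.

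**Assumptions.** Log-normal values, with a CV of 20-60%. The article gives no expected CV. Its only variability figure, 20%, is an interim stopping threshold.

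**Scale.** The log-scale SD is s = √ln(1 + CV²). Arithmetic mean ÷ geometric mean = exp(s²/2) = √(1 + CV²). For a ratio F/M, the expected mean of F/M times the expected mean of M/F is exp(s²) = 1 + CV², where a scale that inverts would give 1.

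**Precision.** The 95% CI for a geometric mean of six is the estimate ×/÷ exp(t × s/√6), with t = 2.571 on 5 df.

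| CV | s | arithmetic ÷ geometric | mean(F/M) × mean(M/F) | 95% CI factor, 5 df |
|---|---|---|---|---|
| 20% | 0.198 | 1.02 | 1.04 | 1.23 |
| 30% | 0.294 | 1.04 | 1.09 | 1.36 |
| 40% | 0.385 | 1.08 | 1.16 | 1.50 |
| 60% | 0.555 | 1.17 | 1.36 | 1.79 |

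**Pooled variance.** Sub-study 2 has two groups of six, so 12 − 2 = 10 residual df and t = 2.228. The factor is exp(2.228 × 0.385/√6) = 1.42 at CV 40% and exp(2.228 × 0.555/√6) = 1.66 at CV 60%. Sub-study 1 has four groups, so 24 − 4 = 20 df and t = 2.086, giving 1.39 and 1.60, but only if the log-scale variance is similar at 2 h and 8 h.

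**Which CV is plausible?** In sub-study 2, blood is taken at delivery, so time since the last dose is not controlled. Three doses a day means 8 h between doses, or two half-lives, so the maternal level falls fourfold under simple exponential decline. With sampling uniform over 8 h, this alone gives the maternal level a CV of about 39%. The CV of the ratio depends on how closely cord levels follow maternal levels, which the article does not say.

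**Arithmetic intervals.** In 400,000 simulated log-normal samples of six, a nominal 95% t-interval built from the arithmetic mean and SD covered the true mean 93.9% of the time at CV 30% and 92.0% at CV 50%. Mean − 2 SD was below zero in 2% and 32% of samples respectively.

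**Pooling 2 h and 8 h.** Assume simple decline between the two times with a 4 h half-life. Levels then differ by 2^(6/4) = 2.83-fold. Set the means to 1 and 1/2.83 = 0.354:

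- Overall mean = (1 + 0.354)/2 = 0.677.
- Between-time variance = ((1 − 0.354)/2)² = 0.104.
- Within-time variance at CV 20% = 0.04 × (1 + 0.125)/2 = 0.0225; at CV 30% = 0.09 × (1 + 0.125)/2 = 0.0506.
- Pooled CV = √(0.104 + 0.0225)/0.677 ≈ 53%, and √(0.104 + 0.0506)/0.677 ≈ 58%.

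So a within-time CV of 20-30% would be reported as 53-58%. Fetal levels may lag behind maternal ones, so the true inflation could differ.

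**The case against.** The strongest reply is that the plan's list is wider than its arithmetic part and is not exclusive. It also contains n, the median, minimum and maximum. The median does not depend on scale, the range of six values shows most of the spread, and a reader can build an interval from n, mean and SD. A reader might infer that the plan hides its imprecision; it does not. It leaves precision unstated, and an arithmetic mean is still a valid description.

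A reader might also infer, from the Discussion's statement that the trial "should allow to determine the effective maternal dosage to be used in the subsequent phase III efficacy study", that a biased mean ratio would set the phase III dose. The article does not say so. Under the Statistical analysis plan, the measured concentrations go into the PBPK model, and that model is to predict the dose.

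Three further replies stand:

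- This is an article. Intervals and model details may sit in a full plan that is not shown, so the missing interval alone is no finding.
- The ratio is primary only in sub-study 2, where pooling gives 10 df.
- At CV 20-30% the scale effect is small beside the sampling error from six women.

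The absence of a placebo is a stated design choice, and the two doses will be shown side by side, so an unadjusted contrast can be read off. The dose-only grouping may also be loose wording, since the interim rule for sub-study 1 works with four groups.

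The replies do not remove the arithmetic scale, which is stated explicitly for pharmacokinetic outputs, or the grouping, which as written merges two randomised sampling times.

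**Conclusion.** The point holds as a minor one about stated analysis choices. The arithmetic mean and SD are poorly suited to the concentrations and the sub-study 2 ratio. The effect is about 2-4% at CV 20-30% and 8-17% at 40-60%, and the mean ratio depends on the direction in which it is written. As worded, sub-study 1 summaries pool 2 h and 8 h samples, which under the decline assumption is a larger distortion than the scale. Six women determine a geometric mean to about ×/÷1.23 (CV 20%) to ×/÷1.79 (CV 60%), and the stated summaries leave the reader to work this out.

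All sizes rest on log-normality and on CVs that the article does not give. The material does not support saying that the primary estimate is invalid, that imprecision is concealed, or that dose selection is biased.

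**What to change.** In the Statistical analysis plan section:

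1. For concentrations and ratios, keep n, median and range, and add the geometric mean, geometric CV and 95% CI.
2. Take these from a model of the log value with the randomised groups as factors: dose and sampling time (all four groups) in sub-study 1, dose in sub-study 2. Pool the variance in sub-study 1 only if it is similar at 2 h and 8 h.
3. State that sub-study 1 pharmacokinetic summaries are by dose and sampling time.
4. For Doppler and vital signs, add the baseline-adjusted 75 mg minus 25 mg difference with its 95% CI, as description and without tests.

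The cost is a few sentences and a few lines of code, with no extra data or patients. The downside is small: the model assumes approximate log-normality and a common variance, which six women per group can check only roughly. The retained median and range guard against that.
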